### Data Management

Data management will be performed by an independent external organization (Micron, Inc.) in accordance with a predetermined data management plan. Data will be collected and linked at multiple time points for each participant. Study investigators, including sponsor-affiliated authors, will not access study data before database lock. After lock, the final dataset will be transferred to an independent statistician within the external organization who has no financial or organizational relationship with the developer and will conduct all analyses. Because the external organization lacks medical expertise in pediatric amblyopia, investigators will help interpret the independently analyzed results and prepare the manuscript. The investigator group will make decisions about reporting and publishing study findings. However, once locked, the dataset cannot be modified; sponsor-affiliated authors cannot alter study data or analysis outputs. The final study report, including results and interpretation, will undergo review by the institutional ethics committee, and the manuscript will undergo independent peer review. These external oversight layers enhance transparency and safeguard research objectivity.

## Results

This study will begin on January 1, 2026, at 3 medical institutions in Japan. Patient enrollment will run from January 1, 2026, to September 30, 2026. The data analysis will begin on October 1, 2026, and the results will be reported by March 31, 2027.

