**Methods:**

This is a multicenter, open-label, prospective, randomized controlled trial that will be conducted at 3 centers in Tokyo, Japan. Pediatric patients aged 3-10 years with anisometropic, strabismic, or refractive amblyopia will be enrolled. Participants will be assigned 1:1 to a VR app group or a control group. The VR app group will use the VR app at home for 1 hour per day for 6 months. The control group will undergo conventional occlusion therapy with an eye patch for 6 months. Each group will comprise 15 participants (30 participants in total). Ophthalmologic examinations will be performed at baseline and at weeks 4, 8, 12, 16, 20, and 24. The primary endpoint will be the change in the best-corrected visual acuity in the amblyopic eye from baseline to week 12. Secondary endpoints will include changes in best-corrected visual acuity, stereopsis, and ocular deviation through week 24. We will also assess treatment adherence, defined as the ratio of the cumulative actual treatment time to the cumulative prescribed time; record adverse events, and evaluate usability in the VR app group. Longitudinal changes in outcome measures will be analyzed using a mixed-effects model.

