**Results:**

Participant enrollment will start from January 1, 2026, to September 30, 2026. The data analysis will begin on October 1, 2026, and the results will be reported by March 31, 2027.

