### Study Setting

This multicenter, open-label, randomized controlled trial is scheduled to be conducted from January 1, 2026, to March 31, 2027. Patients will be enrolled at 3 medical institutions: Toho University Omori Medical Center (Tokyo, Japan), Teikyo University Hospital (Tokyo, Japan), and the CS Eye Clinic (Tokyo, Japan).

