### Study Procedures

Figure 2 illustrates the study enrollment procedure. After obtaining informed consent, pediatric patients will be randomly assigned to either a VR app group, which will undergo amblyopia treatment using the VR app for pediatric patients with amblyopia combined with full refractive correction glasses, or a control group, which will undergo amblyopia treatment based on occlusion treatment with an eye patch combined with full refractive correction glasses [24]. Patients assigned to the VR app group will use the VR app for amblyopia at home for 1 hour per day for 6 months, in combination with full refractive correction glasses. Patients assigned to the control group will follow occlusion therapy with an eye patch for 6 months, also wearing full refractive correction glasses, and the duration of eye patch use will be determined by the prescribing physician. Both groups underwent ophthalmological examinations on the first day of the trial and at weeks 4, 8, 12, 16, 20, and 24. Ophthalmological examinations will include measurements of visual acuity, intraocular pressure, strabismus angle, stereopsis, refractive error, and corneal curvature. Only the VR app group will perform a digital stereopsis test using the VR app once per week and complete a usability questionnaire on the VR app at weeks 2, 12, and 24. The week 2 visit conducted only for the VR app group is intended to confirm that the study participants, particularly those unfamiliar with VR devices, are using the VR app correctly and facilitate their continued appropriate use. Only the control group will record their daily duration of eye patch use in a diary. Study participation will end for both groups after the 24-week visit.

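### The stated analysis start of 1 October 2026 cannot be reconciled with enrolment to 30 September 2026, 24-week follow-up and analysis only after database lock

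*Protocol article*

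**What the plan says.** The calendar appears twice in the protocol article.

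- **Results section:** "Patient enrollment will run from January 1, 2026, to September 30, 2026", followed by "The data analysis will begin on October 1, 2026, and the results will be reported by March 31, 2027".
- **Abstract, Results:** "Participant enrollment will start from January 1, 2026, to September 30, 2026", and again "The data analysis will begin on October 1, 2026".

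The follow-up and analysis rules stand elsewhere.

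- **Abstract, Methods:** "The primary endpoint will be the change in the best-corrected visual acuity in the amblyopic eye from baseline to week 12".
- **Study Procedures:** "Study participation will end for both groups after the 24-week visit".
- **Study Setting:** the trial is open-label and "scheduled to be conducted from January 1, 2026, to March 31, 2027".
- **Data Management:** investigators "will not access study data before database lock". The sentences that follow matter more here. The final dataset passes to an independent statistician after lock, that statistician runs all analyses, and the locked dataset cannot be changed.
- **Sample Size and Statistical Analyses:** primary and secondary analyses follow intention-to-treat and use all data collected before withdrawal.

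The article describes no interim analysis, staged lock or separate week-12 lock.

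**The concern.** Analysis is dated one day after the last child may enrol. Such a child has her first outcome visit at week 4, the primary endpoint at week 12 and the final visit at week 24, all after that date. Someone working to the printed date would have two options. One is to analyse data that are still accruing in an open-label trial, which conflicts with the rule that analysis follows lock. The other is to lock on 1 October 2026 and shut out later visits, which conflicts with the intention-to-treat commitment and with the stated follow-up.

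The point is worth settling before outcome data accumulate, because a comparison by arm on partial data cannot be undone. The article also presents lock as part of its protection against influence from sponsor-affiliated authors, so the timetable should not cut across it.

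**Working it through.** **Inputs**

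- Enrolment: 1 January to 30 September 2026 (Results; Abstract). Counting both ends, this is 273 days.
- Stated analysis start: 1 October 2026. Reporting by 31 March 2027 (Results).
- Study period: to 31 March 2027 (Study Setting).
- Primary endpoint: week 12 = 84 days. Last visit: week 24 = 168 days (Abstract, Methods; Study Procedures).
- Target: 30 children, of whom 24 are required before the dropout allowance (Sample Size and Statistical Analyses).
- Assumption: baseline is on the day of enrolment and visits fall on their nominal day. A later baseline or late visits would push every date back.

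**Step 1. Can the stated start be reproduced?** The earliest date with complete data is the last enrolment date plus the follow-up time.

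- Week 12: 30 September 2026 + 84 days = 23 December 2026, which is 83 days after 1 October 2026.
- Week 24: 30 September 2026 + 168 days = 17 March 2027, which is 167 days after 1 October 2026.

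Neither gives 1 October 2026. The printed date fits the full enrolment window neither for the week-12 endpoint alone nor for the whole dataset.

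**Step 2. Do the end dates fit?** 17 March 2027 falls before 31 March 2027, so the study period contains the last possible visit. From 17 to 31 March 2027 is 14 days. If a child is enrolled on the last permitted day, cleaning, lock, analysis and reporting share those 14 days.

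**Step 3. Who would be incomplete on 1 October 2026?** Working backwards:

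- 1 October 2026 − 84 days = 9 July 2026. Children enrolled from 10 July to 30 September (83 days) have not reached week 12.
- 1 October 2026 − 168 days = 16 April 2026. Children enrolled from 17 April to 30 September (167 days) have not reached week 24.

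The article gives no accrual pattern, so the share is shown as a range:

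| Accrual (assumed) | Lacking week 12 | Lacking week 24 |
|---|---|---|
| All enrolled by 16 April | 0% | 0% |
| Uniform over 273 days | 83/273 = 30%, about 9 of 30 | 167/273 = 61%, about 18 of 30 |
| All enrolled after 9 July | 100% | 100% |

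In the uniform case, 30 − 9 = 21 children would have reached week 12. That is below the 24 the article requires, before any dropout.

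**Step 4. What would make 1 October 2026 workable?** The last child would have to enrol by about 16 April 2026 for complete week-24 data, or by about 9 July 2026 for complete week-12 data. Both are well before the stated close of enrolment.

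**The case against.** The strongest reply is that the timeline is a short list of dates, while Data Management sets an explicit operating rule. Where the two conflict, the rule would probably prevail and the date would slip. That is fair. A reader might infer that the trial plans an early look at the data, that late enrollees will be dropped from the primary analysis, or that the lock safeguard fails. The article supports none of these. It describes no interim analysis and no such exclusion, and its intention-to-treat and lock provisions point the other way.

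A second reply is that the window is only an outer limit. If all 30 children were enrolled by mid-April 2026, complete data could exist by 1 October. This also stands. It would therefore be too strong to say that no lock is possible by that date, or that a given number of children must be incomplete. The 14-day interval likewise applies only if enrolment runs to its last day.

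A third reply is that the study period does contain all follow-up. It does, and the study-end date is not itself in error.

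It might also be said that data analysis here means preparatory work. The article does not say so, and it places all analyses after lock.

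What remains is that enrolment through its full window, 24-week follow-up, analysis only after lock and a 1 October 2026 start cannot all be true. Because the date appears in both the Abstract and the Results section, it is unlikely to be a slip in one place.

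**Conclusion.** The concern holds as an internal contradiction in dates. If enrolment uses its stated window, the analysis start is 83 days too early for the last week-12 visit and 167 days too early for the last week-24 visit. The reporting date is then tight, at 14 days after the last visit, but not impossible on the calendar alone.

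The share of children affected on 1 October 2026 is not fixed by the article. The figures of about 30% (week 12) and 61% (week 24) rest on uniform accrual and are one scenario in a range from about 0% to 100%. The contradiction does not depend on that assumption, only on enrolment staying open as stated.

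This is a scheduling statement that is wrong as written. It does not alter the endpoint, the estimator, the planned sample size or the error rate, and it is not evidence that an early analysis is intended.

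**What to change.** Replace the 1 October 2026 date, in both the Abstract and the Results section, with wording to this effect: *analysis begins only after database lock, following the last participant's week-24 visit (no later than about 17 March 2027 if enrolment closes on 30 September 2026), with no comparison of outcomes by arm before lock.*

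Then make the end dates workable in one of two ways:

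- move the reporting date later, and the study end too if it is meant to include reporting; or
- close enrolment earlier. Each week taken off the window adds a week to the 14 days now left before 31 March 2027.

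If a separate week-12 analysis is intended, state it, with its own lock and its own rules on who may see the results while follow-up continues. It should start no earlier than the last week-12 visit, which is 23 December 2026 under the current window.

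The cost is a correction of dates, with either somewhat later reporting or a shorter enrolment window in which to recruit 30 children.

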## Discussion

Pediatric amblyopia can cause an irreversible reduction in visual acuity and has a profound impact on the quality of life. The conventional therapeutic approach, comprising full refractive correction and occlusion of the healthy eye, has established efficacy. However, the substantial psychological and physical burden imposed on affected children predisposes them to poor adherence and compromises treatment effectiveness, thereby undermining the overall outcomes of amblyopia therapy. Therefore, therapeutic modalities that minimize the burden on pediatric patients and concurrently enhance patient adherence and therapeutic efficacy in the treatment of amblyopia are warranted. This protocol paper outlines a multicenter clinical trial designed to evaluate the therapeutic efficacy of a VR app for pediatric amblyopia. The implementation of VR app–based amblyopia training has the potential to improve treatment outcomes by enhancing adherence through gamification and augmenting therapeutic efficacy via hand-eye coordination.

 VR-based digital therapeutics are increasingly recognized as promising therapeutic modalities for the management of pediatric amblyopia. In contrast to traditional treatment modalities, VR systems can independently modulate the visual input to each eye, thereby facilitating binocular training, which is regarded as critical in amblyopia therapy [38]. Furthermore, game-based amblyopia training that leverages gamification strategies to engage children’s interests is expected to enhance treatment adherence [39]. The objective of this study is to evaluate the therapeutic efficacy of a VR app for pediatric patients with amblyopia, utilizing the distinctive features of VR, in comparison with conventional occlusion therapy using an eye patch on the healthy eye. The VR app delivers game-based tasks that incorporate active bodily movements via hand-tracking controllers. The execution of these tasks necessitates hand-eye coordination. The combination of hand-eye coordination exercises with occlusion therapy in the healthy eye has the potential to augment visual recovery in the amblyopic eye through both direct visual stimulation and facilitation of neuroplasticity [40]. Unlike eye patch occlusion, which entirely blocks visual input to a healthy eye, this method permits simultaneous binocular training, offering the potential for greater visual improvement than conventional amblyopia treatments [41]. The demonstration of the efficacy of VR-based amblyopia training with a VR app in pediatric patients with amblyopia could introduce a novel therapeutic option that integrates the established benefits of occlusion therapy with improved adherence through gamification, promotion of neuroplasticity and visual recovery via hand-eye coordination, and additional visual gains through binocular training. Collectively, these features may drive a paradigm shift in amblyopia treatment.

Several studies have reported the efficacy of VR-based amblyopia training. One study incorporating the VR-based therapeutic device Luminopia One (Luminopia, Inc.) used a method wherein the contrast of streaming content presented to the healthy eye was reduced to encourage viewing with the amblyopic eye. Over a 12-week treatment period, significant improvements in visual acuity and stereopsis were observed, accompanied by high treatment adherence [19,42,43]. As an early example of a VR system, the Interactive Binocular Treatment system, a VR gaming platform employing a stereoscopic display and personal computer, was reported as early as 2006. Using this system, patients underwent treatment once or twice a week for approximately 20 min per session. In a cohort with a mean total treatment duration of 4.4 hours, an average improvement of 10 letters in logMAR visual acuity was achieved [44]. Additional VR-based approaches have been described, such as a photo-hunt game that requires the detection of inconsistencies between images presented to the 2 eyes [45] and NEIVATECH, a serious game–based system intended for binocular training in amblyopia that employs dichoptic presentation of images with differential contrast in a VR environment to implement perceptual learning tasks [41]. Each of these gaming systems seeks to achieve amblyopia training by projecting distinct visual stimuli onto the amblyopic and healthy eyes, thereby enhancing adherence through gamification. Contrastingly, the VR app for pediatric patients with amblyopia used in this study is intended to deliver, in addition to visual stimulation–based amblyopia training and binocular training akin to prior VR-based interventions, the promotion of neuroplasticity via tasks requiring hand-eye coordination. Accordingly, the VR-based SaMD for pediatric patients with amblyopia used in this study may yield superior therapeutic outcomes compared with conventional VR-based amblyopia training systems.

This study has certain limitations. First, despite the explicit inclusion criteria specifying participants with anisometropic, strabismic, or refractive amblyopia and a BCVA of ≤0.5 logMAR in the amblyopic eye, heterogeneity in disease severity, underlying etiology, and associated comorbidities may influence therapeutic outcomes. Second, interindividual differences in age, prior exposure to VR devices, and degree of familiarity may have affected both adherence and therapeutic response, especially during the initial phase of the study. To minimize the influence of such heterogeneity, participants allocated to the VR app group underwent an interim visit at week 2—prior to the first ophthalmologic assessment at week 4—during which VR app usage was reviewed to facilitate the proper continuation of treatment, even among participants with limited prior experience using VR systems. Third, the extended use of the VR app carries the potential risk of adverse effects, including VIMS and asthenopia. Our prior safety evaluation of the VR app in adults revealed no VIMS- or vision-related adverse events [18]. However, data on the long-term use of VR apps in pediatric populations remain limited, and the occurrence of adverse events could potentially affect treatment adherence and diminish the therapeutic efficacy of amblyopia management. Fourth, while amblyopia therapy in clinical settings is generally expected to extend beyond the 6-month duration of this study, this protocol does not permit the evaluation of long-term efficacy, posttreatment sustainability of therapeutic benefits, or the risk of amblyopia recurrence. Upon the completion of this study, an extension study is being conducted to allow interested participants to continue treatment with the VR app. The implementation of such a study with an extended follow-up would facilitate the assessment of long-term therapeutic efficacy and safety, persistence of treatment effects, and the likelihood of amblyopia recurrence. Fifth, the VR app–based stereopsis test used here was newly developed without formal validation. From a visual psychophysics perspective, this task uses a 4-alternative forced-choice design with size-constancy adjustments to reduce monocular cues. However, the extent of monocular cue elimination remains unverified. The floor and ceiling disparity levels of this stereotest are undetermined. Therefore, the stereopsis outcomes should be interpreted as preliminary. We included an in-headset stereopsis measure as it may provide a practical way to assess stereopsis under intervention conditions and enable monitoring between clinic visits, with potential utility for future clinical implementation and remote assessment in telemedicine.

In conclusion, a VR app may overcome the limitations of conventional amblyopia training by offering a highly effective therapeutic alternative, thereby facilitating a paradigm shift in amblyopia management. Future confirmatory clinical trials are required to delineate the efficacy and limitations of the VR app and to determine its potential integration into standard treatment strategies for pediatric amblyopia.
